### Participant timeline {13}

The participant timeline is shown in Table 1.

**Table 1 Tab1:** Study visits of the REDUCE trial. *NRS*, Numeric Rating Scale; *PSS*: patient satisfaction score; *GCS*, Glasgow Coma Scale score; *LOS*, length of stay; *PACU*, postoperative care unit; *PONV*, postoperative nausea and vomiting; *HR*, heart rate; *MAP*, mean arterial pressure; *AEs*, adverse events; *SAEs*, serious adverse events

	Study period											
	Enrollment	Allocation	Post allocation									
Time point	Preoperative	0 d	surgery	2 h	4 h	8 h	12 h	16 h	20 h	1d	2d	Discharge
Enrollment												
Eligibility screen	X											
Informed consent	X											
Allocation		X										
Interventions												
Scalp nerve blocks with bupivacaine		X										
Scalp nerve blocks with bupivacaine plus 4 mg dexamethasone		X										
Assessments												
Baseline variables	X	X	X									
Intraoperative data			X									
The duration of analgesia										X	X	
NRS score				X	X	X	X	X	X	X	X	
GCS score				X	X	X	X	X	X	X	X	
PSS				X	X	X	X	X	X	X	X	
LOS												X
PONV				X	X	X	X	X	X	X	X	
Bradycardia				X	X	X	X	X	X	X	X	
Hypotension				X	X	X	X	X	X	X	X	
Emergence delirium				X	X	X	X	X	X	X	X	
HR and MAP			X									
Occurrence of AEs and SAEs			X	X	X	X	X	X	X	X	X	X

### Sample size {14}

Based on previous studies [19–21, 43] and our clinical practice, the average duration of analgesia after supratentorial craniotomy was approximately 600 min with a standard deviation (SD) of 240 min for patients who received scalp nerve blocks with a local anesthetic alone (the control group). A difference of 60 min in average duration of analgesia is considered the minimally clinically significant difference. Sample size calculation will be performed based on the hypothesis that the duration of analgesia in the patients receiving scalp nerve blocks with local anesthetics and 4 mg dexamethasone (the DEX_4mg_ group) will be a least 30% longer than that in the control group. Based on this assumption, we will need 70 patients per group for a power of 90% and an *α* error of 0.05; to compensate for an attrition dropout rate of 10%, 78 patients will be needed in each group and the total sample size will be 156 patients in the REDUCE trial.

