### Trial design {8}

This study is a prospective, single-center, parallel-group randomized controlled, superiority trial. The planned study has been registered at ClinicalTrials.gov under the identifier NCT04648358. See Fig. 1 for the flow chart. Additional File 1 shows the Standard Protocol Items: Recommendations for Interventional Trials (SPIRIT) checklist for study protocols.

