## Assignment of interventions: allocation

### Sequence generation {16a}

SPSS software version 25 will be used to carry out sample randomization with a 1:1 ratio to one of the two groups by a statistical assistant, who will not be involved in patient assessments.

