## Statistical methods

### Statistical methods for primary and secondary outcomes {20a}

Normality and homogeneity of the data distribution will be evaluated using the Shapiro Wilkinson test. Baseline characteristics, when they consist of descriptive variables with a normal distribution, will be described using the mean ± SD. Data with a skewed distribution will be presented as the median with the 25th and 75th percentiles. Dichotomous and categorical data will be described as frequencies and percentages. Group comparisons will be performed by using Student’s *t* test or the nonparametric Wilcoxon-Mann-Whitney test for quantitative variables and Pearson’s chi-squared test or Fisher’s exact test for categorical variables. NRS score and GCS at different time points will be analyzed with repeated measures analysis of variance (ANOVA) using time as the between-subjects factor. Details of statistical analysis will be fixed, at the latest, in the statistical analysis plan that will be prepared before the database is locked and analysis is commenced. The statistical tests will be 2-tailed and *P* < 0.05 will be considered statistically significant. SPSS software (version 25) will be used to conduct all analyses.

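### The 70 patients per group and the 90% power in the sample size section do not follow from the stated inputs under the planned two-sided test

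*Protocol article*

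**What the plan says.** All inputs are in the protocol article.

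- **Sample size {14}.** Duration of analgesia in the control group is taken as "approximately 600 min with a standard deviation (SD) of 240 min". The dexamethasone group "will be a least 30% longer than that in the control group". The section also says: "A difference of 60 min in average duration of analgesia is considered the minimally clinically significant difference". It then derives the number from the 30% assumption: "we will need 70 patients per group for a power of 90" per cent, with an alpha of 0.05. Allowing for 10% dropout gives 78 per group and 156 in total. The section names no test, no sidedness and no null value.
- **Statistical methods for primary and secondary outcomes {20a}.** "The statistical tests will be 2-tailed", with significance at P < 0.05. Quantitative variables are compared by Student's t test or the Wilcoxon-Mann-Whitney test.
- **Trial design {8}.** A "randomized controlled, superiority trial", with no margin given.
- **Sequence generation {16a}.** Allocation "with a 1:1 ratio to one of the two groups".

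**The concern.** A standardised difference of 180/240 = 0.75 is large, and 90% power for it at a two-sided 5% level needs far fewer than 70 per group. Taking 60 min as the target (60/240 = 0.25) needs far more. The printed number lies between the two and matches neither.

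The stated power is what readers use to judge what the trial can detect. Here 90% is not the power of the planned test for either difference that the section names. If the 70 came from a different hypothesis or a one-sided level, the sample size section and the analysis section describe different tests, and the protocol should say which one applies.

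**Working it through.** **Inputs.** SD 240 min in both arms (the protocol gives an SD for the control group only, so equality is an assumption); equal arms; alpha 0.05; power 90%. Differences: 0.30 × 600 = 180 min (the stated hypothesis) and 60 min (the stated minimal important difference).

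**Formula.** Normal approximation: n per group = 2 × [(z_α + z_β) × SD / difference]², with z_β = 1.2816 and z_α = 1.9600 two-sided or 1.6449 one-sided. The t-distribution figure is the smallest n whose noncentral-t power reaches 90%.

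**Step 1: the plan's own figure.**

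- 180 min, two-sided: 2 × (3.2415 × 240/180)² = 37.4, so 38 per group (t: 39).
- 180 min, one-sided: 2 × (2.9264 × 240/180)² = 30.4, so 31 (t: 32).
- 60 min, two-sided: 2 × (3.2415 × 240/60)² = 336.2, so 337 (t: 338).

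None of these is 70.

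**Step 2: other readings of the 180-min hypothesis**, two-sided 5%, 90% power.

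| Variant | n per group |
|---|---|
| Wilcoxon inflation (relative efficiency 0.955 to 0.864) | 41 to 46 |
| SD proportional to the mean (240 and 312) | 51 |
| Log-normal, coefficient of variation 0.4 | 46 |

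A time-to-event formula with hazard ratio 1/1.3 needs more than 600 events in total. For 180 min to require 70 per group two-sided, the SD would have to be about 326 min (t) to 329 min (normal), against the stated 240.

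**Step 3: what does give 70.** Take an effective difference of 180 − 60 = 120 min, one-sided at 5%: 2 × (2.9264 × 240/120)² = 68.5, so 69 (t: exactly 70). The same difference two-sided at 5%: 2 × (3.2415 × 240/120)² = 84.1, so 85 (t: 86).

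**Step 4: dropout.** 70/0.9 = 77.8, so 78 per group and 156 in total. This step is correct; the mismatch lies in the 70.

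**Step 5: power that 70 per group actually give.** The standard error of the difference is 240 × √(2/70) = 40.6 min. Two-sided 5% t test:

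| True difference | Null | Power |
|---|---|---|
| 180 min | 0 | 99.3% |
| about 132 min | 0 | 90% |
| 60 min | 0 | 31% |
| 180 min | 60 min | 83.6% |

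The 90% point follows from 3.2415 × 40.6 = 131.5 min (about 132 with t), which is 22% of 600. If the SD scales with the mean (240 and 312, an assumption), the standard error is √((240² + 312²)/70) = 47.0 min and power for 180 min against zero is 96.7%.

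**The case against.** The strongest reply is that the discrepancy is in the safe direction. The section ties the number to the 30% assumption, and for that hypothesis 70 per group give more power than claimed. This stands, and it limits the weight of the point.

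Three stronger readings are tempting, and the document does not support them.

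- **That the trial was sized as a one-sided test against a 60-min margin.** The match in Step 3 is exact and uses every figure in the section, so it is a plausible origin. But nowhere is 60 min called a margin or a null value, and the design is plain superiority. A one-sided test of a 120-min effect against zero is arithmetically identical. The origin remains an inference.
- **That the trial is underpowered because power for 60 min is 31%.** Sizing on an expected effect larger than the minimal important difference is a common design choice. The section does not claim 90% power for 60 min.
- **That success is undefined, or must mean a lower confidence limit above 60 min.** The design and analysis sections read as an ordinary two-sided comparison against no difference. A rule on the confidence limit would add a criterion that the protocol does not contain, and interpretation rules may sit in the analysis plan, which is not shown.

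The reply does not rescue the printed figure. An analysis plan can add detail, but it cannot make 180 min, SD 240, 90% power and a two-sided 5% level give 70. If a margin or a one-sided level lies behind the number, it conflicts with the two-tailed rule in the statistical methods section.

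**Conclusion.** The point holds as a wrong stated figure. Under the planned two-sided 5% test, the stated inputs require 39 evaluable patients per group for 90% power, not 70; conversely, 70 per group give about 99% for the stated 180 min. The conclusion rests on a t test with equal arms and an SD of 240 min in both. Letting the SD grow with the mean, or allowing for the Wilcoxon-Mann-Whitney test, moves the required number to between 41 and 51 and does not close the gap.

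The error does not threaten the trial: its 30% hypothesis is more than adequately powered. Only if a 60-min margin was really the hypothesis does the correction go the other way, to about 84% power at a two-sided 5% level, with 86 evaluable per group needed for 90%.

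**What to change.** Keep 156 patients. In the sample size section, state the null value, the sidedness and the formula or software routine used, so that it agrees with the statistical methods section. Then restate the power in one of two ways.

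1. **Null of no difference, as the analysis section reads now.** With 70 evaluable per group, a two-sided 5% t test and an assumed SD of 240 min in both arms, power is about 99% for 180 min (about 97% if the SD scales with the mean), 90% for about 132 min and 31% for 60 min. Label these figures as conditional on the SD and the t test.
2. **Null of a 60-min gain, if that was the intention.** Write that null into the analysis section and give power for a true difference of 180 min as about 84% at a two-sided 5% level.

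The cost is wording in the protocol and analysis plan, before database lock, with no change in recruitment. Under the second option the stated power falls from 90% to about 84%.

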### Recruitment {15}

If the team providing care considers the patient eligible for this study, they can refer the patient to the study researcher. Informed consent will be required from all patients before inclusion in the study and each participant will be informed that their participation would be voluntary and they will be able to withdraw from the study at any time. Patients will be screened and randomly assigned to a study group once scheduled for elective craniotomy under general anesthesia.

## Assignment of interventions: allocation

### Sequence generation {16a}

SPSS software version 25 will be used to carry out sample randomization with a 1:1 ratio to one of the two groups by a statistical assistant, who will not be involved in patient assessments.

### Concealment mechanism {16b}

To maintain blinding, an opaque, sealed, sequentially numbered envelope will be assigned to each patient and will be generated and opened by an independent research fellow who is not involved in patient evaluations.

### Implementation {16c}

After obtaining written informed consent and before surgery, a random envelope will be opened by an independent research investigator who will not be involved in any stage of this trial. Eligible participants will be assigned to either the control group or the DEX_4mg_ group. The random allocation number assigned will be recorded in an electronic chart.

## Assignment of interventions: blinding

### Who will be blinded {17a}

Participants, surgeons, and nurses will be blinded to the treatment assignment, along with the outcome assessors and data analysts. A clinical resident who is not involved with group allocation will be responsible for follow-up assessments as a part of daily clinical practice.

### Procedure for unblinding if needed {17b}

The envelope will be kept separately from the patient’s CRF and opened when the doctors need information about the patient’s treatment in any potentially harmful situation.

## Data collection and management

### Plans for assessment and collection of outcomes {18a}

After obtaining written informed consent, baseline data, including age, sex, BMI, intraoperative opioid dose, operation time, anesthesia time, surgical site, tumor types, and tumor size, will be collected by an independent researcher. The PCA press will be recorded by an electronic memory system in real time. The information of PCA press including the first press of PCA demand button and the cumulative amount of sufentanil consumption can be directly extracted. In order to ensure postoperative analgesia quality, an acute pain management team will monitor the pain pump remotely and deal with problems, such as congestion and battery drain, on time. An independent clinical resident who is not involved with the group allocation will complete a follow-up at 2, 4, 8, 12, 16, 20, 24, and 48 h after surgery.

### Plans to promote participant retention and complete follow-up {18b}

The patients will receive extensive information about study procedures and follow-up plans. Once a patient is enrolled or randomized, the researcher will make all reasonable efforts to follow the patient throughout the study period.

However, patients are still allowed to stop at any time during the study and are not obliged to give a reason to discontinue.

### Data management {19}

All information specified by the protocol will be collected and recorded on the CRF during the trial by the investigators or by designated representatives. The completed CRF will be reviewed and signed by the investigator or by a designated subinvestigator. An explanation will be provided for any missing data. An annual summary of the progress of the trial will be submitted to the accredited IRB.

### Confidentiality {27}

An anonymous dataset will be created by encoding each subject’s identity with a digital code. Individual participant data that underlie the results reported in this article, after de-identification (text, tables, figures, and appendices) will be shared.

### Plans for collection, laboratory evaluation, and storage of biological specimens for genetic or molecular analysis in this trial/future use {33}

This trial does not involve collecting, laboratory evaluation and storage of biological specimens for genetic or molecular analysis.

## Statistical methods

### Statistical methods for primary and secondary outcomes {20a}

Normality and homogeneity of the data distribution will be evaluated using the Shapiro Wilkinson test. Baseline characteristics, when they consist of descriptive variables with a normal distribution, will be described using the mean ± SD. Data with a skewed distribution will be presented as the median with the 25th and 75th percentiles. Dichotomous and categorical data will be described as frequencies and percentages. Group comparisons will be performed by using Student’s *t* test or the nonparametric Wilcoxon-Mann-Whitney test for quantitative variables and Pearson’s chi-squared test or Fisher’s exact test for categorical variables. NRS score and GCS at different time points will be analyzed with repeated measures analysis of variance (ANOVA) using time as the between-subjects factor. Details of statistical analysis will be fixed, at the latest, in the statistical analysis plan that will be prepared before the database is locked and analysis is commenced. The statistical tests will be 2-tailed and *P* < 0.05 will be considered statistically significant. SPSS software (version 25) will be used to conduct all analyses.

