## Introduction

### Background and rationale {6a}

Pain is often considered an inevitable outcome of surgery. Postcraniotomy patients have frequently been assumed to experience modest pain among all surgeries. However, current evidence suggests that pain after neurosurgical procedures is more severe than expected [1, 2]. A prospective study of 187 patients demonstrated that pain was common in the first 2 days after major craniotomy, with approximately 70% of patients reporting moderate to severe pain during the 1st postoperative day and 48% of patients complaining of pain scores greater than or equal to 4 on the 2nd postoperative day [2]. Sympathetically mediated hypertension caused by inadequate analgesia may lead to an increased risk of postoperative complications, such as arterial hypertension, intracranial hemorrhage, prolonged hospital stays, and mortality [3]. In addition, undertreated acute postoperative pain may predict the development of chronic pain [4–6]. Therefore, optimal pain management is of great importance for improving postoperative recovery and patient comfort [7].

Opioids are commonly used for postoperative analgesia, but the use of opioids for neurosurgical procedures is limited by potential side effects such as sedation, miosis, nausea, vomiting, and respiratory depression [8]. Multimodal analgesic techniques, such as combining an opioid with supplemental analgesics (including nonsteroidal anti-inflammatory drugs (NSAIDs), scalp infiltration, and scalp nerve blocks), typically result in improved analgesia with concurrent reductions in the incidence of systemic opioid-related adverse effects [8, 9]. The neural tissue of the brain does not contain any pain receptors. Most pain following craniotomy arises from the pericranial muscles and soft tissues of the scalp [10]. Therefore, scalp nerve blocks, which suspend the function of the sensory nerve fibers in the superficial and deep soft tissue layers, can reduce the consumption of analgesic drugs and may enhance early postoperative recovery.

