### Outcomes {12}

#### Primary outcome

The primary outcome will be the duration of analgesia, defined as the time between the performance of the block and the administration of the first press of PCA demand button postoperatively.

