#### Secondary outcomes

The cumulative amount of sufentanil consumption by PCA at 4, 12, 24, and 48 h postoperatively and the number of participants who have no PCA press will also be documented.The NRS (11-point scale in which 0 = no pain to 10 = worst imaginable pain) will be determined at fixed intervals after the procedure, i.e., 2, 4, 8, 12, 16, 20, 24, and 48 h. An NRS score ≥4 will be considered significant or moderate pain. An NRS score ≥7 will be considered severe pain. Meanwhile, the localization of the site of the pain will also be documented.The GCS [40] will be assessed at predetermined intervals after the procedure, i.e., 2, 4, 8, 12, 16, 20, 24, and 48 h.Postoperative observation: postoperative nausea and vomiting (PONV), bradycardia, hypotension, and emergence delirium within 48 h after surgery will be recorded. Vomiting will be defined as the forceful expulsion of gastric contents, and nausea will be defined as an unpleasant sensation associated with the urge to vomit. Bradycardia will be defined as HR< 60 beats/min in at least two instances more than 5 min apart. Hypotension will be defined as any of the following: systolic BP < 90 mm Hg for 5 min or a 35% decrease in mean arterial blood pressure [41]. Emergence delirium will be assessed by the Sedation Agitation Scale (SAS), a 7-point scale on which a higher score represents greater agitation [42]. The time in the PACU and the length of stay (LOS) will be recorded. The LOS will be defined as the number of nights spent in the hospital after surgery. The postoperative data will be collected by reviewing each patient’s medical record.Postoperative satisfaction: Patient satisfaction will be assessed by the patient satisfaction score (PSS) (0 for unsatisfactory to 10 for very satisfactory) at 2, 4, 8, 12, 16, 20, 24, and 48 h after surgery.

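### The primary outcome is a time to first PCA press that some patients may never reach, but the protocol names only complete-data tests and LOCF and does not say how unreached times enter the comparison

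*Protocol article*

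**What the plan says.** All references are to the protocol article.

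- **Primary outcome:** the endpoint is "the time between the performance of the block and the administration of the first press of PCA demand button postoperatively".
- **Secondary outcomes:** sufentanil use through the pump is followed until 48 h after surgery. Patients without any press are foreseen: "the number of participants who have no PCA press will also be documented". No expected share is given.
- **Subject withdrawal criteria** and **Sample size {14}:** patients may leave the study, for instance because they need systemic glucocorticoid after surgery. Attrition of 10% is planned for.
- **Statistical methods {20a}:** "Normality and homogeneity of the data distribution will be evaluated using the Shapiro Wilkinson test". Quantitative variables are then to be compared by Student's t or the "nonparametric Wilcoxon-Mann-Whitney test for quantitative variables". No Kaplan-Meier, log-rank, Cox or other censored-data method is mentioned.
- **Non-adherence and missing data {20c}:** the main analysis is a modified ITT analysis of treated patients, and missing observations are filled by last observation carried forward.
- **Deferral in {20a}:** "Details of statistical analysis will be fixed, at the latest, in the statistical analysis plan", to be prepared before the database is locked.

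**The concern.** The outcome is a time to event with a fixed end of observation. A patient who has not pressed by then has a duration known only to exceed a limit, and so does a patient who withdraws before a first press. Both are right-censored. The named tests take one number per patient, and the protocol does not say what that number is for these patients. LOCF cannot supply it, because a single event time has no earlier value to carry forward.

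The analyst must then choose between dropping such patients and giving them some value, possibly after seeing the data. Patients with no press have the longest analgesia. If dexamethasone makes more patients reach the end without pressing, dropping them removes the effect the trial is looking for. The choice between t and Wilcoxon, if it depends on a normality test of the same data, adds a second data-dependent step to the primary comparison.

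**Working it through.** **1. The plan's own figure.** Sample size {14} gives a control mean of 600 min, SD 240 min, a prolongation of at least 30% (0.30 × 600 = 180 min), a minimal important difference of 60 min, 90% power, α 0.05 and 70 per group. Using n = 2(z_α + z_β)² × SD² / Δ²:

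| Δ (min) | Two-sided n per group | One-sided n per group |
|---|---|---|
| 180 | 38 | 31 |
| 60 | 337 | 275 |
| 180 − 60 = 120 | 85 | 69 (70 with the t distribution) |

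The stated 70 is matched only by the last cell, a reading the protocol does not state. The dropout step is right: 70 / 0.90 = 77.8, so 78. What matters here is that every version is a formula for means with all times observed. None contains events or censoring.

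**2. Can that model hold a no-press patient?** 48 h is 2880 min. Such a patient lies at least (2880 − 600) / 240 = 9.5 SD above the control mean. The planning model has no place for such patients.

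**3. Illustration of what the handling does.** From the protocol: mean 600, SD 240, 30% prolongation, 70 per group, two-sided 0.05. Assumed: Weibull times (shape 2.70, scale 675, which give that mean and SD) and the no-press shares. There were 1,500 runs per scenario, so the simulation error is at most √(0.25/1500) ≈ 1.3 percentage points.

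*Scenario A: no-press 10% in control and 25% with dexamethasone, equal times among those who press.*

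| Handling | Estimated difference | Rejection rate |
|---|---|---|
| No-press patients dropped, t test | about 1 min | about 5% |
| Kept and ranked last, Wilcoxon | – | about 34% |
| Kept as censored, log-rank | – | about 55% |
| 2880 min entered, t test | (0.25 − 0.10) × (2880 − 600) = 342 min | about 64% |

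The same data can give no effect or a difference of several hours.

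*Scenario B: 30% prolongation among those who press, equal no-press shares.*

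| No-press share in each arm | Dropped, t test | Kept and ranked last, Wilcoxon | Kept as censored, log-rank |
|---|---|---|---|
| 10% | 95% | 82% | 58% |
| 20% | 93% | 60% | 31% |
| 30% | 89% | 40% | 17% |

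With equal shares, dropping costs little power. The danger arises when the shares differ, as they may if the block works better in one arm.

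**4. End of observation.** The clock starts at the block, before incision, while the 48 h run from surgery. The end of observation is therefore later than 2880 min on this clock. That does not change the rank or log-rank results, because no-press patients come last either way. It does change any mean built from an entered value. With an assumed 4 h from block to end of surgery, the 342 min becomes 0.15 × (3120 − 600) = 378 min.

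**The case against.** *The Wilcoxon test already copes.* If everyone is followed to the same end, giving all no-press patients any value above the observed times ranks them last, which is a valid rank analysis. This stands, so it would be too strong to say that the named tests cannot be used. But the protocol does not state this convention, and it does not cover patients who withdraw early.

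*The t test would collapse.* A reader might infer this, because entering 48 h for 10/20/30% of patients raises the pooled SD to about 707/909/1032 min and cuts t-test power to about 28/15/11% in Scenario B. The documents do not support it as the expected result. If the test is chosen by the normality check, Shapiro rejected in 100% of runs at these shares, so the Wilcoxon would be used. In Scenario A the t test with 48 h entered is in fact the most powerful of the four.

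*The no-press share is unknown.* This stands. The background reports "approximately 70% of patients reporting moderate to severe pain during the 1st postoperative day", and one might infer that about 30% will never press. That figure is pain severity in a cited cohort. Here patients may press on request at any score, staff will encourage them to, and observation lasts 48 h.

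*Details are left to the SAP.* The wording in {20a} covers quantitative variables in general, and the link from normality test to choice of test is inferred from sentence order. Both are fair. Yet the section is headed as covering the primary outcome, no other test is offered for it, and the class of test and LOCF are already fixed for fully observed data. A deferral of details does not undo that.

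**Conclusion.** The point holds. The protocol defines a time to event, foresees patients without the event and patients who withdraw, and fixes methods that do not say how either enters the primary comparison.

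The size depends on an unknown no-press share and on whether it differs between arms. In the 10% versus 25% illustration, dropping no-press patients leaves about 5% rejection, the nominal error rate, against about 34% or 55% when they are kept. With equal shares of 10/20/30% and a 30% prolongation, the rank test that keeps them has about 82/60/40% power. These figures rest on Weibull times and assumed shares; they are not forecasts for this trial.

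The working might also suggest that one censored-data test is the right one. It does not: log-rank does better in Scenario A and the rank test in Scenario B. What matters is that one is named in advance.

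**What to change.** Before database lock, state for the primary outcome:

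1. Kaplan-Meier curves from block to first press, with one pre-specified two-sided test, either log-rank or a generalised Wilcoxon.
2. Patients with no press stay in the analysis, censored at the end of the 48 h postoperative observation and measured on the clock that starts at the block.
3. Patients who withdraw before a press are censored at their last pump record.
4. Medians and/or a restricted-mean difference are reported with a 95% CI, the restriction time being stated on the same clock.
5. The normality-dependent choice of test and LOCF do not apply to this outcome.

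The cost is SAP wording. The PCA system already records presses electronically in real time, so no new data are needed. The effect will no longer be a simple difference in means, and the stated 90% power will depend on the no-press share. The sponsor should show power over a plausible range of that share.
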